### Objectives

The study’s primary objective is to test whether the Cedar Project mHealth intervention reduces vulnerability to HIV among young Indigenous people who use drugs, measured by using an HIV propensity score described below. Our secondary objectives are to test the specific ways the mHealth intervention may reduce vulnerability to HIV by exploring HIV risk behaviours, resilience, psychological distress, access to drug-related services, and connection to culture among participants over the course of the study.

We hypothesize that participants receiving the intervention will seek help from Cedar Case Managers to navigate barriers to drug-related services, housing, cultural supports, and health care. Also, we hypothesize that participants will use the phones as tools to connect with other supports and sources of strength in their lives, including family, work, culture, and services. Thus, we hypothesize that the intervention will help young people to work towards goals related to their own health and well-being, supporting them to reduce HIV risk.

### Outcome measures

#### Primary outcomes

The primary outcome (Table 1) is HIV risk, measured by an HIV propensity score assessed at the 6-month time point. Previous analyses of Cedar Project data with respect to HIV infection have identified several factors as associated with HIV infection, including recent injection drug use, high-frequency drug use, needle sharing, and participation in sex work [12]. Logistic regression of risk factors for prevalent HIV infection at study recruitment will provide coefficients to combine these four risk variables into a single primary outcome measuring propensity for HIV infection. Mean change in HIV propensity score from baseline to 6 months will be used to determine the impact of the intervention on HIV vulnerability.

**Table 1 Tab1:** Outcome measures

Outcome measure	Specific variable	Analysis metric	Hypothesis (intervention > control)	Type	Analysis
Primary					
HIV propensity (6 months)	HIV propensity score	Mean change - HIV propensity score	Decrease in HIV risk	Continuous	T test
Secondary					
HIV propensity (12 months)	HIV propensity score	Mean change - HIV propensity score	Decrease in HIV risk	Continuous	T test
HIV vulnerability	Injection drug use	Mean change - proportion injection	Decrease in injection	Binary	χ^2^ test
	High-frequency injection	Mean change - proportion frequent injection	Decrease in injection frequency	Binary	χ^2^ test
	Needle sharing	Mean change - proportion needle sharing	Decrease in needle sharing	Binary	χ^2^ test
	Participation in sex work	Mean change - proportion sex work	Decrease in sex work	Binary	χ^2^ test
Resilience	Connor-Davidson Resilience Scale (CD-RISC)	Mean change - CD-RISC score	Increase in resilience	Continuous	T test
Psychological distress	Symptom Checklist-90-R (SCL-90-R)	Mean change - SCL-90-R score	Decrease in psychological distress	Continuous	T test
Access to drug-related services	Opioid substitution therapy (OST)	Mean change - proportion accessed OST	Increase in access OST	Binary	χ^2^ test
	Needle exchange (NX)	Mean change - proportion attended NX	Increase in access NX	Binary	χ^2^ test
	Safe injection facility (SIF)	Mean change - proportion visited SIF	Increase in access SIF	Binary	χ^2^ test
	Drug treatment	Mean change - proportion seeking treatment	Increase in seeking treatment	Binary	χ^2^ test
	Tried to quit using drugs	Mean change - proportion trying to quit	Increase in trying to quit	Binary	χ^2^ test
Connection to culture	Participation in traditional ceremonies	Mean change - proportion participated in traditional ceremony	Increase in access to ceremony	Binary	χ^2^ test
	Frequently living by traditional culture	Mean change - proportion lived by traditional culture	Increase in traditional culture	Binary	χ^2^ test

All variables refer to behaviour in the 6-month period preceding the interview. All variables are measured as mean change in proportion or score from baseline

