##### HIV vulnerability

Although the effect of the intervention on HIV risk will be assessed in the primary analysis, we will also analyze the effect of the intervention on specific behaviours. Several self-reported binary measures will be used to determine the effect of the intervention on HIV vulnerability in the previous 6-month period, including injection drug use in the past 6 months, high-frequency (daily or more) drug use, needle sharing, and participation in sex work. These measures will be ascertained from Cedar Project questionnaires collected every 6 months as part of the main Cedar Project cohort. HIV vulnerability will be assessed at baseline, 6 months, and 1 year.

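### The 6-month primary score looks back over the whole follow-up, so stopping part-way does not show on the injecting, sharing or sex-work items, and the 12-month score that could show it is restricted by time on the intervention

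*Protocol article*

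**What the plan says.** Under Primary outcomes, the endpoint is HIV risk "measured by an HIV propensity score assessed at the 6-month time point". Its ingredients are "recent injection drug use, high-frequency drug use, needle sharing, and participation in sex work", and a logistic regression "will provide coefficients to combine these four risk variables into a single primary outcome measuring propensity for HIV infection". The contrast between arms is also fixed there: "Mean change in HIV propensity score from baseline to 6 months will be used to determine the impact of the intervention on HIV vulnerability".

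The look-back is set in the Table 1 footnote: "All variables refer to behaviour in the 6-month period preceding the interview". The HIV vulnerability section confirms it for these behaviours ("Several self-reported binary measures will be used to determine the effect of the intervention on HIV vulnerability in the previous 6-month period") and lists them as "injection drug use in the past 6 months, high-frequency (daily or more) drug use, needle sharing, and participation in sex work". Table 1 types the four behaviour rows as binary. Study setting puts cohort interviews 6 months apart.

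A 12-month score is listed first among the secondary outcomes. The Secondary outcomes section limits all 1-year analyses to participants with enough follow-up. The section on the 12-month score limits that analysis to participants who had the intervention long enough. The Statistical analysis section, by contrast, promises intention to treat for primary and secondary outcomes in everyone randomised.

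**The concern.** The look-back is as long as the gap between baseline and the primary reading. For an item scored as any act in the window, one episode soon after the start fixes the 6-month answer at yes, whatever happens later.

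The intervention is expected to work gradually, through weekly check-ins, referrals and support: "we hypothesize that the intervention will help young people to work towards goals related to their own health and well-being". Change that builds over weeks or months is the kind a whole-period yes/no item registers poorly. The secondary behaviour items at 6 months share the same window, so they do not help.

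At stake is the interpretation of a null primary result. It could be read as no reduction in HIV vulnerability although some participants had stopped by month 6. The reading best placed to show this, at 12 months, is restricted by something that happens after randomisation and only in one arm.

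**Working it through.** **The plan's own figure.** The Sample size section gives 78 per arm for d = 0.40, one-sided 0.05, 80% power. Check: n = 2(1.645 + 0.842)² / 0.40² = 2 × 6.185 / 0.16 = 77.3; the t-based calculation gives 77.97. Both round up to 78. With 20% attrition, 78 / 0.80 = 97.5, so 98, consistent with the target of 100. The sample size is correct on its inputs and is not in dispute.

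**Coding of one any-act item** (injecting, sharing or sex work), for a participant coded yes at baseline and interviewed exactly 6 months after the start, so that the window is months 0 to 6:

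- No act after baseline: yes, then no. Credited as a fall.
- Stops in week 3: yes, then yes. No change.
- Stops in month 4: yes, then yes. No change.
- Never stops: yes, then yes. No change.

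The last three are indistinguishable on that item. This follows from the definition alone.

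**What can still move the 6-month score:**

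- the high-frequency item, whose scoring across the window is not described;
- participants with no act after baseline;
- prevention of new behaviour among people coded no at baseline.

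**The same item at 12 months**, with the window at months 6 to 12: participants who stop in week 3 or month 4 and stay stopped are coded no. Those who never stop are coded yes. This is the first reading that separates them.

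**Illustration for one item only.** The documents give no act rates or stopping times. Assume that stopping times are uniform over the 6 months and that acts before stopping follow a Poisson process, with x acts expected over a full window. The share of true stoppers coded as changed at 6 months is (1 − e^(−x)) / x:

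- about one act per 6 months, x = 1: 63%
- one act every 2 months, x = 3: 32%
- monthly, x = 6: 17%
- weekly, x = 26: 4%
- daily, x = 182: about 0.5%

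The range runs from more than half to almost none, depending wholly on an assumed rate. It describes an item, not the score, and does not convert into a loss of power.

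**The case against.** A reader might infer that anyone who stops during the intervention is scored as unchanged on the primary outcome. The documents do not support that. The effect is shown item by item, and the score combines four items and can move by the routes listed above. The binary coding of the score's ingredients is also a reading of two sections together: the Primary outcomes text does not use the word binary for them. The footnote's claim to cover all variables is itself loose, because the SCL-90-R is given a 3-month window. The 6-month window for the four behaviours is nevertheless confirmed separately.

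Interview timing matters too. Outcomes come from routine cohort interviews, and no alignment with the start of the intervention is stated. With an interview at month 8, for example, the window would open at month 8 − 6 = 2, and people who stopped before then would be credited. The exact statement holds for an aligned interview.

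A reader might also want to discount d = 0.40 and quote a reduced power. That is not justified. The Sample size section introduces d directly after naming the 6-month score, so it is already the assumed effect on that score. Shrinking d with the standard deviation held fixed would also be wrong, because fewer people changing also reduces the spread of change.

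Finally, any risk behaviour over a period is a legitimate and openly stated quantity, the 12-month score is prespecified, and the Limitations section concedes that the outcomes may not capture the intervention's full impact. All this stands. It limits the size of the point. It does not remove the insensitivity of the items, nor the restriction on the 12-month analysis.

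**Conclusion.** The point holds as partial insensitivity. With an aligned interview, three of the four ingredients of the primary score cannot register stopping that follows any act after baseline, and nothing in the article gives a shorter recall window or a current-status version. The direction is towards no difference. The size for the whole score cannot be computed from the document, and no power figure should be quoted.

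The 12-month score is the first that can show sustained stopping begun in months 0 to 6. Restricting it by time on the intervention is a post-randomisation selection that cannot apply equally to controls, and it sits badly with the stated intention-to-treat analysis of secondary outcomes.

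It would be tempting to conclude that the primary time point should move to 12 months. The documents do not support that: enrolment has begun in an open trial, and only 6 months of intervention are guaranteed, so the move would exchange one dilution for another.

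The conclusion rests on the binary coding of the score's ingredients, an interview about 6 months after the start, and any-act scoring of injecting, sharing and sex work.

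**What to change.** Keep the 6-month score as primary, and make two changes:

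1. In the Secondary outcomes and HIV propensity (12 months) sections and in Table 1, analyse the 12-month score by allocated arm in all randomised participants, using the routine cohort interviews. Remove the condition on time on the intervention. Name this analysis the first-ranked secondary and estimate it in one repeated-measures model with the 6-month score.
2. Describe the 6-month score as any risk behaviour during the first 6 months, and state that a null result there does not show that behaviour did not change.

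The cost is wording and analysis. Both arms are already interviewed every 6 months, so no visit or question is added. There are two drawbacks. Attrition will be greater at 12 months. Some late starters will be partly off the intervention during months 6 to 12: the intervention period is 16 months, so anyone starting after month 16 − 12 = 4 reaches 12 months after it ends. Both should be acknowledged when the 12-month result is reported. The second change costs nothing.

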#### Secondary outcomes

The potential benefits of the supportive mHealth intervention are broad. As a result, multiple secondary outcomes are of interest. These were selected through consultation with academic and community partners and are part of routine Cedar Project data collection. They fall under five categories: HIV risk, resilience, psychological distress, access to drug-related services, and connection to culture. For all secondary outcomes, the effect of the mHealth intervention will be measured as change in the outcome from baseline to 6 months. Participants with sufficient follow-up time will contribute to analyses of all outcomes at the 1-year time point to determine longer-term effects of the intervention.

##### HIV propensity (12 months)

Participants who received the intervention for a sufficient length of time will contribute to a secondary analysis of change in HIV propensity at 1 year to determine longer-term effects of the Cedar Project WelTel mHealth intervention. The HIV propensity variable will be generated by using the same approach used for the primary outcome.

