**Methods:**

The Cedar Project WelTel mHealth study is a multi-site Zelen pre-randomized trial to measure the effect of a two-way supportive text-message intervention to reduce HIV vulnerability among young Indigenous people who use illicit drugs in two Canadian cities. The trial is nested within the Cedar Project, an ongoing cohort study addressing HIV and hepatitis C vulnerability among young Indigenous people who use drugs in Vancouver and Prince George, British Columbia. The Cedar Project Partnership, an independent body of Indigenous Elders, leaders, and health/social service experts, governs all aspects of the study. Two hundred participants will be followed over a 16-month period, with HIV propensity score at 6 months as the primary outcome. Secondary outcomes include HIV propensity at 1 year, HIV risk, resilience, psychological distress, access to drug-related services, and connection to culture measured at 6 months and 1 year. Primary analysis is by intention to treat.

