#### Comparison group

One hundred Cedar Project participants who meet the eligibility criteria will be allocated to serve as the cohort comparison group, stratified on the same variables used to select the intervention group. Participants randomly assigned to the control group will continue as Cedar Project participants under usual circumstances. This group of cohort controls will not be required to provide any additional data to the study beyond that which they provide in semi-annual follow-up interviews as participants in the main Cedar Project study.

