### The intervention

The Cedar Project WelTel mHealth intervention being evaluated is a structured mobile-phone initiative to connect young Indigenous people who use drugs with Cedar Case Managers in a community-based setting. The intervention consists of a package of supports, including a mobile phone and cellular plan, weekly two-way text messaging, and support from Cedar Case Managers. The intervention will be implemented over a 16-month period, and all participants will receive the intervention for a minimum of 6 months.

Cedar Case Managers include Indigenous and non-Indigenous nurses and Cedar Project staff members who have extensive frontline outreach experience with young Indigenous people who use drugs in Prince George and Vancouver. Cedar Case Managers follow a “culturally safe” approach that acknowledges both trauma and strengths and includes an explicit focus on the critical roles of cultural assets and safe relationships with care providers in HIV risk reduction [31].

Participants allocated to receive the intervention will be provided with a cellular phone at the start of the study. Each phone is pre-programmed with several phone numbers for emergency and health-related services relevant to the study site. During the study period, participants will receive a monthly cellular plan that includes unlimited calling and texting within Canada, but no data. We made an explicit decision to include long-distance calling and texting to provide the opportunity for participants to connect with family and loved ones living in home communities and elsewhere in Canada. If phones are lost or stolen, participants will be eligible to receive one replacement. If two phones are lost, the participant may bring their own sim card-enabled cellular handset to use with the study monthly cellular plan.

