### Statistical analysis

The analysis and reporting of the results will follow the CONSORT (Consolidated Standards of Reporting Trials) guidelines [44]. Descriptive statistics of socio-demographic, historical/lifetime trauma, sex- and drug-related HIV vulnerabilities, and health-related variables will be presented to assess comparability of the intervention and control groups. Mean (standard deviation) or median (quartiles) will be used for continuous variables and count (percentage) for categorical variables. Our primary analysis to evaluate the effect of the mHealth intervention on HIV prevention will be by intention to treat (ITT) for primary and secondary outcomes among all randomly assigned participants according to the study group to which they were originally allocated. Student’s *t* tests and chi-squared tests will be used to determine differences in the mean change in proportions or scores from baseline at 6 months or 1 year between the two study arms. If baseline characteristics are found to be substantially different between the two study arms, we will adjust for these factors by using regression models. In addition, we will conduct a secondary analysis by using a modified ITT approach including only participants who agreed to participate in the intervention making up the intervention group (excluding over-sampled participants who did not receive the intervention). To minimize the risk of bias introduced in our modified ITT analysis, we propose to use complier average causal effect (CACE) analysis [45]. This approach will allow us to retain the initial random assignment by taking into account two subgroups within the group pre-randomized to receive the intervention (those who did and did not actually receive the intervention) and then helping us to identify a similar subgroup of control participants who could have been expected to receive the intervention had it been offered [45]. By comparing expected and observed outcomes in these subgroups, we will obtain a less biased estimate of effect of the intervention [45]. Missing data will be approached by using multiple imputation. An up-to-date version of R statistical software will be used to conduct all analyses [46]. All tests will be two-sided; *P* values of less than 0.10 will be considered significant. We plan to conduct four predetermined exploratory subgroup analyses that may help to tailor the intervention for specific high-need populations, including comparisons by gender, city, injection drug use, and urban versus rural. Statistical methods similar to those described above for whole-group analyses will be conducted for primary and secondary outcomes. All subgroup results will be reported, regardless of significance. Inferences will be hypothesis-generating, given concerns related to multiple comparisons and lower power to detect an effect in subgroups.

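### The 12-month HIV propensity analysis selects people by how long they received the intervention, a rule that can filter only one arm and conflicts with the stated ITT analysis

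*Protocol article*

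**What the plan says.** The article gives three statements on who enters the 12-month HIV propensity analysis.

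- **The section on the 12-month outcome** makes inclusion depend on how long the intervention was received: "Participants who received the intervention for a sufficient length of time will contribute to a secondary analysis of change in HIV propensity".
- **Secondary outcomes:** "Participants with sufficient follow-up time will contribute to analyses of all outcomes at the 1-year time point". Inclusion depends on follow-up time, with no mention of receipt.
- **Statistical analysis:** the primary analysis is by ITT "for primary and secondary outcomes among all randomly assigned participants according to the study group to which they were originally allocated". The tests compare "differences in the mean change in proportions or scores from baseline at 6 months or 1 year between the two study arms".

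The outcome is on the secondary list: the abstract states "Secondary outcomes include HIV propensity at 1 year, HIV risk, resilience", and Table 1 gives it a t test of mean change. On the control arm, the Comparison group section says: "Participants randomly assigned to the control group will continue as Cedar Project participants under usual circumstances". On timing, the section on the intervention says: "The intervention will be implemented over a 16-month period, and all participants will receive the intervention for a minimum of 6 months".

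**The concern.** A rule based on duration of intervention is applied after randomisation and depends on what happened to each person after allocation. In a Zelen design only the invited arm can be reached or missed, accept or refuse, and enrol early or late. The rule therefore cannot be applied in the same way to the two groups that the t test compares.

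At stake is whether a 12-month difference can be read as an effect of allocation. If invitees with long exposure would have changed differently from the other invitees even without the intervention, a difference from controls appears when there is no effect. The article recognises this mechanism: its Discussion says that leaving out people who refuse could bias the comparison, and its Limitations say that the modified ITT analysis may suffer from selection bias. A duration rule goes further than the modified ITT set, because it also removes people who agreed but enrolled late. This outcome is the planned longer-term look at the construct used for the primary outcome.

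**Working it through.** **Step 1. Apply each rule to each group.**

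| Group | Duration of intervention received | Sufficient follow-up time | ITT, all randomised |
|---|---|---|---|
| Invited, enrolled early | in | in | in |
| Invited, enrolled late | out | depends on calendar time | in |
| Invited, refused or not reached | out | depends on calendar time | in |
| Control | cannot be applied | depends on calendar time | in |

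The first rule differs from the other two and is the only one that depends on receipt. Taken strictly, it leaves no control group. Taken as a filter on those who can meet or fail it, it acts on the intervention arm alone. It is also the more specific text for this outcome, so an analyst could reasonably follow it.

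**Step 2. The article's own sample size, as a check.** The inputs are d = 0.40, one-sided 0.05, 80% power and 1:1 allocation (Sample size section). The normal formula is n = 2 × ((1.645 + 0.842)/0.40)² = 77.3, rounded up to 78. The t-based solution is 77.97, also 78. With 20% attrition, 78/0.80 = 97.5, so 98, consistent with the planned 100 per arm. These figures concern the 6-month primary outcome and are not affected. No figure is given for 12 months.

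**Step 3. Who could have 12 months of intervention?** The inputs are 140 allocated to invitation and 100 to be enrolled (Intervention group section), a 16-month programme and a 6-month minimum. The accrual pattern is not stated. Here sufficient is taken to mean the full 12 months, which is also an assumption.

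- Latest entry that allows 12 months: 16 − 12 = month 4.
- Latest entry that allows 6 months: 16 − 6 = month 10.
- Even enrolment over 10 months: 4/10 × 100 = 40 people, and 40/140 = 29%.
- All 100 enrolled by month 4: 100/140 = 71%.

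Slower early accrual would fall below 29%. A lower threshold for sufficient would raise that figure, but not above 71% as long as 100 are enrolled.

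**Step 4. What selection could do (illustration only).** Let f be the share of the 140 retained and g the assumed difference in mean change, in SD units, between retained and excluded invitees when the intervention has no effect. Suppose that all 100 controls are kept and there is no attrition. Controls then resemble the whole invited group, so bias = (1 − f) × g, with SE = √(1/(140f) + 1/100). The false-positive rate is for a two-sided test at 0.10, the level in the Statistical analysis section.

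| Retained (f) | SE | g = 0.2: bias, rate | g = 0.3: bias, rate | g = 0.5: bias, rate |
|---|---|---|---|---|
| 100 of 140 (0.71) | 0.141 | 0.06, 0.13 | 0.09, 0.16 | 0.14, 0.27 |
| 70 of 140 (0.50) | 0.156 | 0.10, 0.17 | 0.15, 0.25 | 0.25, 0.48 |
| 40 of 140 (0.29) | 0.187 | 0.14, 0.20 | 0.21, 0.31 | 0.36, 0.60 |

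For example, with f = 40/140 and g = 0.3, bias = 0.714 × 0.3 = 0.214 and 0.214/0.187 = 1.145. The rate is 1 − Φ(1.645 − 1.145) + Φ(−1.645 − 1.145) = 0.31. With g = 0 there is no bias and the rate is 0.10. A negative g gives the same rates with the opposite sign of bias. Neither f nor g is given in the article.

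**The case against.** The strongest reply is that the sentence is loose wording for a calendar limit. In a 16-month programme with a 6-month minimum, late enrollees cannot have 1-year data, and the Secondary outcomes section says so in terms of follow-up time and with the same purpose of showing longer-term effects. The Statistical analysis section applies ITT to secondary outcomes and to 1-year comparisons, and keeps analysis by receipt in a separate modified ITT and CACE analysis. This may well be what was meant. It does not remove the conflict: the text specific to this outcome states a different rule and does not point to the modified ITT or CACE analysis.

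The precise meaning of sufficient, and how dates are anchored for controls, may also stand in the full protocol or SAP. That is fair, and their absence here is not the point. The point is that the article states two different inclusion rules for one outcome, and only one of them can be reconciled with ITT.

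A reader might infer four stronger things, none of which the document supports:

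- **That every 1-year outcome is affected.** The exposure wording covers 12-month HIV propensity only. The other 1-year outcomes fall under the follow-up rule, which treats both arms alike.
- **That all controls are kept at 1 year.** This is not stated. It is an assumption of the illustration above.
- **That the bias favours the intervention because early enrollees are more stable.** Nothing says that early enrolment predicts falling risk, and the recruitment routes include street outreach and word of mouth as well as office visits.
- **That about 40 recipients, with correspondingly low power, is the expected position.** It is one end of a range that depends on unstated accrual. A legitimate calendar limit would also reduce numbers, so loss of power is not evidence of the ITT breach.

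**Conclusion.** The point holds for one secondary outcome, HIV propensity at 12 months. As written, its inclusion rule selects after randomisation on exposure, can act on the intervention arm only, and contradicts both the ITT statement and the follow-up rule for 1-year analyses. The conflict of wording is certain.

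The consequence is exposure to selection bias of unknown size and direction. The share of the 140 who would qualify is about 29% under even enrolment over 10 months and up to 71% if all 100 enrol by month 4, with sufficient taken as 12 months. The false-positive rates in the working show what assumed differences between retained and excluded invitees would do; they are not estimates for this trial. The 6-month primary analysis and the sample size are not touched.

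**What to change.** Replace the inclusion rule in the section on HIV propensity (12 months) with one rule for both arms:

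- Include every randomised person whose common time zero, such as the date of randomisation, is early enough for a 1-year assessment by the data cut-off, regardless of whether or for how long the intervention was received.
- Analyse by ITT as allocated, with the multiple imputation already planned for missing interviews.
- Use the same rule in the Secondary outcomes section, and define sufficient follow-up there in months from that time zero.
- Confine any 12-month estimate based on receipt or duration to the supplementary modified ITT and CACE analysis, and label it as such.

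This needs no new data and no change to the sample size. It does cost something in interpretation. The 12-month ITT estimate will be more diluted, because some invitees will have had short or no exposure by then. For instance, if time zero were the release of the invitation list, a person enrolled at month 9 would have about 12 − 9 = 3 months of intervention at the 1-year point. The estimate then describes the effect of being allocated to invitation, not of a year of intervention. The choice of time zero also fixes which interview counts as baseline, so it should be settled before the 12-month data are analysed.
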